### Inclusion and exclusion criteria

The participants will be selected according to the following criteria: (1) first episode of unilateral stroke (ischemic or hemorrhagic) resulting in walking deficits, (2) injury time equal to or greater than 6 months, (3) age between 20 and 70 years old, (4) ability to walk without personal assistance indoors (Functional Ambulation Category (FAC) scores equal to or greater than 3) [33], (5) walking speed on the ground equal to or less than 0.9 m/s (limited community walking), according to the categorization proposed by Fulk *et al*. [34] (2017), and (6) ability to understand and obey simple motor commands.

Exclusion criteria will include (1) pregnancy; (2) show instability in cardiac conditions (uncontrolled heart disease) or heart failure (New York Heart Association (NYHA) scores of at least 3 (or both) [35]; (3) presenting other clinical conditions affecting gait; (4) presenting pain or severe discomfort which hinders performing the proposed activities (or both); (5) presenting decompensation of systemic arterial pressure, systolic and diastolic values [36]; and (6) HR above the submaximal values allowed during training, maintained even after pauses, calculated by means of the formula [HRsub = 0.75 × (220 − age)] [37], where HRsub = submaximal HR.

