### Randomization and blinding

Randomization sequence will be generated by computer [38], and three groups with blocks of 12 participants will be considered. This stage will be conducted by a researcher not involved in the study. This researcher will keep the randomization list confidential until the end of the study and will organize the allocation in sequentially numbered opaque envelopes. These envelopes will be sealed, and the randomization sequence will be according to the coding that will be created for study groups (control, experimental 1, and experimental 2).

The content of each envelope will be revealed only at the beginning of the training of each patient by study therapists in order to maintain allocation confidentiality. The same therapists involved in control group training will perform training in the experimental groups. Sample characterization measures and outcome measures will be evaluated by masked researchers in relation to group allocation. These researchers will be the same as those who enrolled participants in the study.

Only variables that will be collected during the training will be evaluated by study therapists (non-blind). Statistical analysis will be performed by one researcher, who will be blind to the allocation of patients in groups. Data will be tabulated with a predetermined encoding by another blinded evaluator, who will also check data (range check for data values). The present protocol has been prepared in accordance with relevant items from the SPIRIT (Standard Protocol Items: Recommendations for Interventional Trials) checklist (Additional file 1) and the SPIRIT figure (Fig. 1).

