## Evaluation procedures

The researchers will be trained before data collection procedures to ensure the reliability of measurements. It is important to highlight that these researchers will remain blind to group allocation throughout the study period.

Previously contacted patients with stroke or those who spontaneously search for the study will be evaluated according to inclusion criteria at our laboratory, where they will be informed about the research objectives and procedures to be carried out. Once they agree to participate in the study, they will be asked to sign a consent form.

The participants will first be submitted to a general approach to obtain clinical, demographic, and anthropometric data, and other measures of sample characterization will also be collected. Furthermore, the following outcome variables will be evaluated: gait speed, functional capacity, and muscle torque. Participants will subsequently remain at rest, sitting for at least 15 min. During this period, quality of life will be evaluated. Lastly, cardiovascular parameters will be obtained (at rest).

Outcome measures will be collected again at the end of the interventions (post-training), after 30 days of the end of the interventions (short-term follow-up), and after 1 year of the end of the interventions (long-term follow-up). Adverse events will be evaluated at follow-up.

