## Experimental protocol

Participants will undergo all procedures described above on the day of initial evaluation and then the first intervention session will begin. Patients will be allocated according to groups in which they were randomly assigned. The group will be revealed when the envelope is opened by therapists.

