**Fig. 2 Fig2:**
[figure not shown]
System for gait training: Gait Trainer System 2

The training protocol will follow what was used in a previous study, involving patients with subacute stroke, since the protocol used was safe and capable of increasing gait speed and distance covered on a treadmill [53]. In the first training session, participants will undergo a few minutes of treadmill training for familiarization and will be instructed to hold onto the anterior treadmill bar with their non-paretic hand to provide stability. The treadmill speed will be selected as the “maximum comfort”, meaning the maximum tolerated by the individual, while adequate posture is maintained throughout gait cycle without any compensation or muscle fatigue.

From the second session, participants will be encouraged to withdraw support from their non-paretic hand over the treadmill bar. In the following session, participants will be encouraged to increase the treadmill speed according to individual tolerance. Participants will be encouraged to achieve maximum speed at the beginning of the session. After reaching that speed, it will remain constant throughout the session. This procedure will be repeated at the beginning of all subsequent sessions.

The treadmill training sessions will last 30 min, and two small rest periods (about 3 min) will be allowed in the 10th and 20th minutes, which will not be counted in the total duration of the session. During these pauses, the therapists will monitor cardiovascular parameters, effort perception, and pain. However, HR will be monitored throughout the session so as not to exceed the maximum submaximal values (75% of maximum frequency) and so that training can occur by maintaining target frequency of 50% of maximum HR [14].

Before training (in rest), individuals will be assessed regarding cardiovascular parameters and will be reassessed in the 1st and 5th minutes after the end of the session by the study therapists. The control group will be submitted to training by treadmill during a 30-min session without inclination three times per week for 6 weeks.

Experimental group 1 - treadmill gait training with inclination of 5%

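### Exclusion criterion 6 is, on its natural reading, met only in training sessions after allocation is revealed: it is a post-randomisation exclusion listed as an eligibility rule, and it sits badly with the intention-to-treat statement

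*Protocol article*

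**What the plan says.** The section Inclusion and exclusion criteria of the protocol article gives as exclusion criterion 6 "HR above the submaximal values allowed during training, maintained even after pauses". The limit is 75% of age-predicted maximum heart rate and has the same formula in all three arms.

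Other sections fix when this can be observed:

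- **Evaluation procedures** describes the assessment before allocation. Its heart rate component reads "Lastly, cardiovascular parameters will be obtained (at rest". No exercise test before allocation is described.
- **Experimental protocol** gives the order: "Participants will undergo all procedures described above on the day of initial evaluation and then the first intervention session will begin".
- **Randomization and blinding** says "The content of each envelope will be revealed only at the beginning of the training of each patient by study therapists". It also says that variables collected during training are recorded by therapists who are not blind.
- **Study groups** (control group training, text after Fig. 2) describes the pauses: "two small rest periods (about 3 min) will be allowed in the 10th and 20th minutes". Heart rate is monitored throughout each session against the same ceiling.
- **Statistical analysis** plans intention-to-treat for dropouts, using each participant's last available data.

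**The concern.** An eligibility criterion should be settled before allocation. One that depends on how a person responds to the assigned treatment is a post-randomisation event, whatever list it appears in. If it is applied as an exclusion, people leave the comparison because of something that happened on their assigned slope, as judged by staff who know the slope. The three groups are then no longer guaranteed to be comparable.

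The slope is the randomised factor, and the Discussion itself describes inclined training as high intensity. It is therefore plausible that the limit is met at different rates in the three arms. With 12 people per arm, a few such exclusions would matter. The Background also asks whether inclined training is safe compared with flat training, and the number of people meeting the limit in each arm bears directly on that question.

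**Working it through.** The plan states no figure for this event, so the main check is the order of events.

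**Step 1: when can the criterion be met?**

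| Stage | Heart rate information | Allocation known? |
|---|---|---|
| Baseline assessment | Resting values | No |
| Envelope opened at start of training | None new | Yes, to therapists |
| Training sessions, with rest breaks at minutes 10 and 20 | Continuous monitoring, with readings at the breaks | Yes, to therapists |

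A heart rate that stays above a training limit despite pauses needs training and pauses. Both occur only in the third row. The schedule is 3 sessions × 6 weeks = 18 sessions with 2 breaks each, so 18 × 2 = 36 breaks per participant, all after allocation.

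**Step 2: does the limit depend on arm?** The limit is 0.75 × (220 − age), and the eligible range is "age between 20 and 70 years old".

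- Age 20: 0.75 × 200 = 150 bpm
- Age 45: 0.75 × 175 = 131.25 bpm
- Age 70: 0.75 × 150 = 112.5 bpm

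It varies with age and not with arm. Apart from chance, any difference between arms in how often it is met must come from the training load or from how therapists apply the rule.

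**Step 3: how many people could be affected?** The documents give no rate, so these are assumptions that only show the range. For a rate p and 12 per arm, the expected number is 12p and the chance of at least one is 1 − (1 − p)^12.

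| Assumed rate: control / 5% / 10% incline | Expected number of 12 | Chance of at least one |
|---|---|---|
| 5% / 5% / 5% | 0.6 / 0.6 / 0.6 | 46% / 46% / 46% |
| 5% / 10% / 20% | 0.6 / 1.2 / 2.4 | 46% / 72% / 93% |
| 10% / 20% / 40% | 1.2 / 2.4 / 4.8 | 72% / 93% / >99% |

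The first row has no expected imbalance. In the others, the inclined arms lose more people. Nothing in the protocol selects among the rows.

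**Step 4: what happens to these people in the analysis?** The text allows two readings.

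- *Excluded as ineligible.* They leave the analysis, and the arms compared are no longer the arms randomised. This contradicts intention-to-treat.
- *Kept as dropouts with the last value.* Gait speed, the 2-minute walk, torque and quality of life are measured at baseline and then not until the end of training. For anyone stopped in between and not assessed again, the last value is the baseline value, so their recorded change is exactly zero. If all others in the arm change by the same amount, a share p of such people multiplies the arm's mean change by 1 − p. A value that could have been measured has been replaced by an assumption.

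The two readings give different analysis sets and can distort the comparison in different directions. The article does not say which applies.

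**The case against.** **Timing.** The reference to training may define the threshold rather than the moment of assessment, and the schedule in Fig. 1 cannot be seen. This is why the point is stated on the natural reading. The mention of pauses, which exist only inside sessions, still makes that reading much the stronger one.

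**Differential removal.** A reader might infer that the criterion does remove more people from the inclined arms. The documents do not show this. Speed is set by individual tolerance in every arm, heart rate is held under the same ceiling, and the incline is introduced gradually, so people walking on the flat may simply walk faster. A difference is plausible, not established.

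**Direction and size of bias.** A reader might also infer that the inclined arms end up enriched with fitter people and so look better. That needs three things the protocol does not give: that these participants are removed rather than carried forward, that the exceedance rates differ, and that a high heart rate marks slower or less fit walkers. Faster walkers could equally have the higher response, and some participants may take beta-blockers. With the last value carried forward, early stops count as no change, which for an improving outcome works against the arm with more stops. No figure in m/s can be supported.

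**Safety data.** The statement "Adverse events will be evaluated at follow-up" might be taken to mean that tolerability information is thrown away. It does not say that adverse events are recorded only then, and effort, pain and cardiovascular readings are taken in sessions. That charge does not stand.

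**Level of detail.** An article may leave follow-up procedures to the full protocol. The point is not that detail is absent: the article itself places a post-allocation event among the exclusion criteria while promising intention-to-treat.

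**Conclusion.** The point holds as a defect of timing and of consistency. On its natural reading, criterion 6 is a post-randomisation exclusion observed by non-blind therapists on the assigned slope, and the intention-to-treat statement does not settle what becomes of the people who meet it. It may act unequally by arm, because the load is randomised under a common ceiling.

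Its size cannot be derived from the documents. What can be said is that each person affected is 1/12 = 8.3% of an arm, and that under the assumed rates above the expected loss runs from 0.6 to 4.8 people per arm. The direction of any bias is unknown. The conclusion rests on two readings of the text: that the pauses meant are the in-session breaks, and that no exercise heart rate test takes place before allocation. This should be corrected, and it is cheap to correct.

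**What to change.** Reconcile the exclusion criteria, the description of the training sessions and the Statistical analysis section. The heart rate limit and its clinical handling stay with the investigators.

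1. State that meeting criterion 6 after allocation does not remove a participant from the trial or from the analysis.
2. Invite these participants to the post-training, 1-month and 1-year assessments, so that measured values replace carried-forward ones where possible.
3. Analyse them in the arm to which they were randomised.
4. Report the number meeting the limit in each arm, using the heart rate data already recorded in sessions.

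The cost is one reworded criterion, a matching sentence in the analysis section, and follow-up of the few people affected. No new measurement is needed.

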## Measures

### Sample characterization measures

Clinical and demographic data: These will be evaluated by filling out a structured identification form about data such as paretic side, stroke type, age, gender, injury time, and drug treatments (including beta-blockers).Ability to walk: This will be evaluated by FAC, which consists of a sensitive and reliable instrument for gait evaluation in stroke patients with hemiparesis [33]. FAC ranks six levels of walking ability according to the amount of physical support required for this task. On this scale, the score can vary from 0 (unable to walk or needs the help of two therapists) to 5 (independent in locomotion).Motor function: It will be evaluated by Fugl–Meyer Scale, which allows us to analyze and quantify sensory-motor function after stroke [39]. Only motor function requirements will be used in this study, and it includes measuring movement, coordination, and reflex activity of the shoulder, elbow, wrist, hand, hip, knee, and ankle. Scores below 50 points indicate severe motor impairment; 50–84, outstanding; 85–95, moderate; and 96–99, mild [40].

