### Outcome measures

Primary outcome measures considered for this study are the following:Gait speed: This will be measured by the 10-meter walking test [41]. This test consists of a simple measure which presents good reliability and reproducibility and is valid to evaluate physical mobility in a clinical or home environment [42].Functional capacity: This will be measured by the 2-min walk test [43]. This test has demonstrated adequate inter- and intra-examiner reliability in patients with stroke and has an advantage compared with the 6- and 12-min walk tests because it presents a time considered efficient and reduces fatigue effects in these patients [44].Cardiovascular parameters: BP will be checked by using a calibrated digital arm sphygmomanometer (Visomat Comfort III^®^, Incoterm, São Paulo, Brazil) on the non-paretic arm. HR will be measured by means of an HR meter (chest belt) (Polar Care^®^, Polar, São Paulo, Brazil). Derived variables such as mean BP, reserve HR, and predicted maximum HR will be calculated from BP and HR measured values. Physiological measures such as BP and HR are non-invasive parameters easily verified by using available devices in clinical practice. Exercise HR has been used as a physical fitness measure after stroke [45], and both HR and BP have been indicated to evaluate the cardiovascular response to exercise in individuals with stroke [14]. Also, peripheral oxygen saturation will be checked by using a pulse oximeter (Palpus 1 SA210, Rossmax, Taipei, Taiwan). Exercise capacity (energy expenditure) in metabolic equivalents (METs) will be estimated from HR by using the HR index (HR_INDEX_) in accordance with the equation developed by Wicks *et al*. [46] for patients with and without heart disease (including those taking beta-blockers).

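### One age-only heart-rate ceiling and target apply to all participants although beta-blocker users are expected, and drug status is neither in the stated analysis nor re-asked at follow-up

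*Protocol article*

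**What the plan says.** **Limit and target.** Exclusion criterion 6 (Inclusion and exclusion criteria) removes participants with "HR above the submaximal values allowed during training, maintained even after pauses", the limit being "calculated by means of the formula [HRsub = 0.75 × (220 − age" in years. The training description for the control group (Study groups), which the inclined groups follow, applies the same limit: "HR will be monitored throughout the session so as not to exceed the maximum submaximal values (75% of maximum frequency" is the ceiling, and the sentence continues with "maintaining target frequency of 50% of maximum HR". Neither rule has a term for drug treatment.

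**Beta-blocker users.** No exclusion criterion names these drugs. Sample characterization measures lists "drug treatments (including beta-blockers" among the baseline items. Outcome measures supports the equation for metabolic equivalents (METs) as being "for patients with and without heart disease (including those taking beta-blockers".

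**Follow-up and analysis.** Heart rate (HR), blood pressure (BP) and METs estimated from HR are among the primary outcomes. Evaluation procedures says that outcome measures are collected again post-training, at 30 days and at 1 year, and that adverse events are evaluated at follow-up. It does not say that drug treatment is asked again. Statistical analysis names a mixed repeated-measures ANOVA across assessments, and t tests or Mann–Whitney tests between groups within each training session. Drug status appears in neither, and Randomization and blinding states no stratification.

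**The concern.** The protocol allows for beta-blockers when HR is used to estimate an outcome, but not when HR sets the training limit. If these drugs lower the HR a person can reach, one bpm limit means different relative efforts in users and non-users. That makes the delivered dose less uniform than the protocol implies, and weakens the limit somewhat in users.

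The second issue is interpretation. Lower HR and BP are the benefits the trial hopes to see (Discussion), and a drug that lowers HR or BP moves these outcomes in the same direction. With 12 per arm, uneven use can shift a comparison of HR or BP levels. A drug started, stopped or changed between baseline and 1 year would move the later values without leaving a trace in the data that the article says will be collected.

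**Working it through.** **Step 1. The limits from the protocol's own formula.** The age range is "age between 20 and 70 years old". Maximum = 220 − age; ceiling = 0.75 × maximum; target = 0.50 × maximum. The ceiling formula is explicit. The target formula is inferred: 220 − age is the only maximum-HR formula given, and the 75% and 50% stand in one sentence. At age 60: maximum 220 − 60 = 160, ceiling 0.75 × 160 = 120 bpm, target 0.50 × 160 = 80 bpm.

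**Step 2. The same bpm in a user.** Relative intensity = bpm / (220 − age − r), where r is the fall in attainable maximum under the drug. The documents give no value, so r = 10, 20 and 30 bpm are assumptions.

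| Age | Target / ceiling (bpm) | Ceiling as % of attainable maximum, r = 10 / 20 / 30 | Target as %, r = 10 / 20 / 30 |
|---|---|---|---|
| 20 | 100 / 150 | 78.9 / 83.3 / 88.2 | 52.6 / 55.6 / 58.8 |
| 50 | 85 / 127.5 | 79.7 / 85.0 / 91.1 | 53.1 / 56.7 / 60.7 |
| 60 | 80 / 120 | 80.0 / 85.7 / 92.3 | 53.3 / 57.1 / 61.5 |
| 70 | 75 / 112.5 | 80.4 / 86.5 / 93.8 | 53.6 / 57.7 / 62.5 |

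For the ceiling to be unreachable at age 60, the attainable maximum would have to be below 120 bpm, a fall of more than 160 − 120 = 40 bpm. That is outside the assumed range.

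**Step 3. Chance imbalance.** The share of users is not in the documents. Take 20%, 30% or 50% of 36 (7, 11 or 18 users) divided at random into three arms of 12 (multivariate hypergeometric). The probability that two given arms differ by at least 3 users is 20%, 28% and 31%. The probability that some two of the three arms do so is 45%, 54% and 53%.

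**Step 4. What an imbalance does to each analysis.** Let the drug lower HR by 10 bpm (assumption), and let one arm have 3 more users than another.

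- Comparison of levels within a session: the arm means differ by 10 × 3/12 = 2.5 bpm from drug use alone. The stated tests do not remove this.
- Baseline-to-follow-up contrast with stable drug use: the 2.5 bpm is present at both times, so the difference in change is 2.5 − 2.5 = 0.
- Baseline-to-follow-up contrast when drugs change: each net participant who starts or stops in one arm and not in the other shifts the difference in change by 10/12 = 0.83 bpm. Three such participants shift it by 2.5 bpm.

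The protocol gives no standard deviation for HR or BP, so these shifts cannot be put on a standardised scale.

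**The case against.** **No contradiction.** An equation chosen to estimate an outcome does not dictate how a training limit must be set. This stands: the sections do not strictly contradict each other. They do leave open how a limit built on age alone applies to participants whose drug use the protocol itself treats as relevant to HR.

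**Other controls on load.** Treadmill speed is the maximum tolerated with adequate posture and no muscle fatigue. Cardiovascular parameters, effort and pain are checked at the pauses in minutes 10 and 20, and unstable cardiac conditions and decompensated blood pressure are exclusions. This also stands. A reader might infer that the ceiling no longer acts as a limit in beta-blocker users. The documents do not support that: under the assumptions above it is reached at 80% to 92% of attainable maximum at age 60, so it acts later rather than not at all.

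**Randomization and baseline contrasts.** Uneven use would be a chance imbalance, and a constant drug effect cancels in the group-by-time contrast. A reader might therefore infer a built-in bias between inclines from the 2.5 bpm figure, but that is a shift in level, not in change. The objection does not reach the session comparisons, where the stated tests involve no baseline contrast, or drug changes after baseline.

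**Silence of a journal article.** A covariate could sit in an analysis plan that is not shown, and a medication question in the full protocol or case report form; the schedule figure is also missing. So it cannot be said that drug status will be ignored. It can be said that the article names its tests and the measures it repeats, and that drug status is in neither.

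**Excluding values after a drug change.** This would condition on an event after randomization. If training lowers BP, responders may be the ones whose drugs are reduced, and dropping them would depart from the stated intention-to-treat approach. This stands and shapes the fix.

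**Conclusion.** The point holds in a limited form. One age-only ceiling, and by inference one target, applies to a sample in which beta-blocker users are expected. The possible effect on intensity is moderate: at age 60, 80% to 92% of attainable maximum at the ceiling instead of 75%, and 53% to 62% at the target instead of 50%, if the drug lowers the maximum by 10 to 30 bpm.

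For the analysis, the exposed parts are the unadjusted HR and BP comparisons within sessions (2.5 bpm for an excess of 3 users in an arm of 12 and a 10 bpm drug effect) and the follow-up results for HR, BP and METs if drugs change. The main group-by-time contrast is largely protected against stable differences in use. The drug effects and user shares are assumptions, so the sizes are illustrative. The uniform limit and the absence of drug status from the stated tests and repeat visits come directly from the text.

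**What to change.** 1. The sponsor should reconcile the exclusion criterion and the training description with the baseline drug item and the METs equation, and state how the HR limits apply to beta-blocker users. That is a clinical decision, and no rule is proposed here.
2. Use baseline beta-blocker use, already collected, as a covariate for the HR, BP and METs outcomes. Do the same for the session HR and BP comparisons, replacing the unadjusted t tests or Mann–Whitney tests by a model with group and beta-blocker use.
3. Re-ask drug treatment at the post-training, 1-month and 1-year visits and report changes by arm. Keep the intention-to-treat analysis primary. Any analysis that leaves out values obtained after a drug change is supportive only, and should be labelled as conditioning on a post-randomization event.

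The cost is one degree of freedom for the covariate in a small trial, and one form question at three visits that already take place. Participants already past a visit can be asked only in retrospect, and this should be noted.
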